### Randomisation

The 12 participating schools are randomly assigned to either the control or intervention cluster. Randomisation is performed prior to the commencement of the study by a researcher unrelated to the study; researchers are blinded to school allocation until after baseline data collection at the relevant school. The schools are informed of their allocated treatment after baseline data collection.

### Interventions

#### Child-based intervention

Unstructured materials are introduced on the school playgrounds to be used during recess. The materials are selected to conform to seven principles: 1. no obvious play value; 2. encourage cooperative, gross motor play; 3. have multiple uses; 4. can be used in challenging, creative and uncertain ways; 5. provide interesting sensory experiences (e.g., from touch or movement); 6. inherent hazards can easily be seen/managed by a child; 7. are, or are made from, re-cycled materials. Examples of items include car tyres, milk crates, and cardboard boxes; in some cases these are reinforced or made more water resistant (e.g., by drilling tyres or covering cardboard with plastic tape). Some items, such as crash mats, are fabricated from recycled objects. All materials are checked for safety characteristics and child-proofed; all meet Australian standards for playground materials. New materials are introduced periodically to replace broken objects or to complement existing objects. Maintenance of the materials is the responsibility of researchers in collaboration with each school community but school staff must agree to remove materials that are broken or being used in unsafe ways.

This intervention runs in each intervention school over 2 terms (13 weeks total), during which time children are able to use and play freely with the items. The materials are for the use of all children at the school, independent of project consent.

#### Adult intervention: Risk Reframing

Teachers and parents of participating children from the intervention schools are asked to participate in a 2-hour group intervention. The adults participate in small "task groups" (*n *= 6-8) as well as large whole-group discussions (*N *= 18-24) to examine their own experiences of free play and their beliefs regarding the benefits and risks associated with active play. Discussions focus on similarities and differences of parents' and teachers' perceptions of the benefits of play, healthy (or manageable) vs. unhealthy risk and the consequences of preventing children from engaging in play and healthy risk taking. Schools are offered compensation for the time the teachers are participating in the sessions.

### Control schools

The control schools participate in standard recess, and they do not have access to the unstructured materials or to risk reframing.

### Outcome measures

The primary outcome measure is children's physical activity, as measured by accelerometers. The secondary outcomes include: self-concept and social skills, social interactions, after school time use and anthropometric measures. All the measurements are performed during one full school week (Table 1).

**Table 1 T1:** Outcome measures and schedule of the study

Outcome	Measure	Data collection	Dependent variable	Baseline	Post-test
BMI	*Stadiometer and scales*	Researcher with child	Height and weight	1 occasion	1 occasion
Physical Activity	*Actigraph accelerometer^1^*	Devices worn by children	Counts, and minutes in sedentary and moderate to vigorous activity	5 days	5 days
	*Activity Diary^2^*	Palm pilots responded on by parents	Activities undertaken after school	4 days	4 days
Social Interaction	*Playground Behaviour*	Video recording	Social behaviour	15 min	15 min
	*SSIS-RS ^3^*	Parent and teacher reports	Social skills and problem behaviour	1 occasion	1 occasion
Self-concept	*PSPCSAYC^4^*	Researcher with child, and teacher reports	Feelings of competence	1 occasion	1 occasion

^1 ^www.theactigraph.com

^2 ^Palm pilot Z22

^3 ^Social Skills Improvement System Rating Scales [61]

^4 ^Pictorial Scale of Perceived Competence and Social Acceptance for Young Children [60]

### Measurements

#### Physical activity during school days

Actigraph accelerometers (GT3X, http://www.theactigraph.com) are worn on the participating children's right hip, on the iliac bone, on top of clothing and fastened with an elastic waist band. A researcher attaches the accelerometers at 9.00 AM and removes them at 3.00 PM for 5 consecutive school days. Movement is measured in three planes at 5 second epochs.

Data are downloaded from the accelerometers using the product-coupled software ActiLife and stored as .dat files to be used in subsequent analyses. To measure the level of physical activity, total accelerometer counts, as well as minutes and percent of time spent in sedentary, light, moderate and vigorous physical activities are calculated, using a custom-made macro ([name]). The cut-points for levels of physical defined by Evenson et al. [58] are used. Accelerometer non-wear time is defined as a count of 0 for 10 consecutive minutes [59].

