**Methods/Design:**

This study protocol describes the design of a 3-year cluster randomised controlled trial (CRCT), in which schools are the clusters. The study consists of a 13-week intervention and 1 week each of pre-and post-testing. We are recruiting 12 schools (6 control; 6 intervention), with 18 randomly chosen participants aged 5 to 7 years in each school. The two intervention strategies are: (1) Child-based intervention: Unstructured materials with no obvious play value introduced to the playground; and (2) Adult-based intervention: Risk reframing sessions held with parents and teachers with the aim of exploring the benefits of allowing children to engage in activities with uncertain outcomes. The primary outcome of the study, physical activity as measured by accelerometer counts, is assessed at baseline and post-intervention. Additional assessments include social skills and interactions, self-concept, after school time use and anthropometric data. Qualitative data (i.e., transcriptions of audio recordings from the risk reframing sessions and of interviews with selected teacher and parent volunteers) are analysed to understand their perceptions of risk in play. The control schools have recess as usual. In addition to outcome evaluation, regular process evaluation sessions are held to monitor fidelity to the treatment.

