### Sample size

Sample size calculation involves deciding on both the number of schools (clusters) and number of children per school. The desired number of schools provides sufficient cluster-level data for subsequent analyses but, at the same time, is manageable in terms of implementation and data collection. We have selected 12 schools (6 control, 6 intervention) to meet these criteria.

The number of children needed per school is estimated by considering the amount of change from the intervention and correcting for the possibility that children at the same school affect one another's activity levels (determined by intra-cluster correlation [ICC]) We estimated the effect size from the intervention conservatively at 0.5 standard deviations (SD) based on a report that young children engage in moderate to vigorous playground activity 26% of the time and that 40% would be a realistic health-promoting target [57].

With *p *= 0.05, power = 80% and an ICC of .04, we require 18 children per school to show that an effect size of 0.5 SD is significant between groups. This reflects a 68% inflation in sample size over the number that would be required if no adjustment were made for cluster effect (64 vs. 108 participants/group).

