#### Data analysis

Primary outcomes (activity levels) will be analysed using intention-to-treat principles. The effectiveness of the intervention for increasing activity, changing social skills and after school activities will be measured at both cluster and individual levels. Mixed-effects multi-level regression (STATA/IC 12, http://www.stata.com), taking clustering and repeated measurement of participants into account, will be used to examine net change from baseline values between groups. At the individual level, multivariate regression will be used to examine the contributions of activity level to changes in self-concept and social skills between groups. Secondary analyses will be conducted to explore subgroup effects (e.g., by sex). In addition, the contribution of potential confounders such as BMI will be explored.

Data from the audio recordings of the risk reframing sessions, parent interviews and field notes kept by project staff will be transcribed either in their entirety or as brief written reports. The resulting qualitative data will be converted to text to be analysed according to an adaptation of Charmaz's [64] approach to social analysis. Initial emergent themes will be identified and data coded for patterns and complexity regarding participants' experiences, actions, beliefs or relationships to risk, assumptions regarding risk, the larger process of which this action or belief is a part, and possible implications of such actions or beliefs for particular actors, institutional forms, parents, families, or children.

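### The only count variable the article derives is a total, which the non-wear rule cannot adjust; the primary count should be expressed per minute of wear

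*Protocol article*

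**What the plan says.** All references are to the protocol article.

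- **Abstract, Methods/Design:** "The primary outcome of the study, physical activity as measured by accelerometer counts, is assessed at baseline and post-intervention".
- **Outcome measures:** the wording is looser, "The primary outcome measure is children's physical activity, as measured by accelerometers". The dependent variables for the accelerometer in Table 1 are "Counts, and minutes in sedentary and moderate to vigorous activity".
- **Physical activity during school days (wear):** "A researcher attaches the accelerometers at 9.00 AM and removes them at 3.00 PM for 5 consecutive school days".
- **Same section (derived variables):** "total accelerometer counts, as well as minutes and percent of time spent in sedentary, light, moderate and vigorous physical activities are calculated".
- **Same section (non-wear):** "Accelerometer non-wear time is defined as a count of 0 for 10 consecutive minutes".
- **Data analysis:** "Primary outcomes (activity levels) will be analysed using intention-to-treat principles".

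Counts therefore appear as a total, and intensity bands appear both as minutes and as a share of time. No count per unit of wear is named, and the article does not say how non-wear enters the count variable. Nor does it say whether the total is per day or per week.

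**The concern.** A non-wear rule exists so that unworn time is not mistaken for inactivity. For sedentary minutes and for percentages of time it can do that, because removing flagged time changes the numerator, the denominator or both. For a sum of counts it does nothing, because the flagged minutes contribute zero whether they are kept or removed. The article thus pairs its headline variable with a data-quality rule that has no effect on it. Table 1 also leaves out percent of time, the only time-standardised measure in the text.

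What is at stake is precision. Differences in wear between children, and between the baseline and post-test weeks, pass straight into the outcome. If wear also changed differently in the two arms, part of the estimated effect would be a wear effect.

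**Working it through.** **The plan's own figure.** The inputs come from the Sample size section: "With *p *= 0.05, power = 80% and an ICC of .04, we require 18 children per school", with an effect of 0.5 SD and six schools per arm.
- Two-sample t-test, two-sided 0.05 and 80% power: 63.8, rounded up to 64 per group.
- Design effect: 1 + (18 − 1) × 0.04 = 1.68.
- 64 × 1.68 = 107.5, rounded up to 108 = 6 × 18 per group.

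The stated 64 and 108 reproduce, and this point does not change them. The same section justifies the effect size by a share of time in moderate to vigorous activity (26% against a target of 40%), which is a time-standardised quantity and not a total.

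**Effect of unworn time on a total.** The window from 9.00 AM to 3.00 PM is 360 minutes a day, or 5 × 360 = 1,800 minutes a week. Let a child accumulate *r* counts per minute, and let *u* minutes be unworn out of a window of *W*. Then total = *r*(*W* − *u*), with or without the zero-run rule. Counts per worn minute = *r*(*W* − *u*)/(*W* − *u*) = *r*. This assumes that unworn time would have been as active as worn time.

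| Unworn time | Fall in that day's total | Fall in a five-day total | Fall in counts per worn minute |
|---|---|---|---|
| 60 min | 60/360 = 16.7% | 60/1,800 = 3.3% | 0 |
| One full day | no daily total | 360/1,800 = 20% | 0 |

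**Noise, under assumptions.** The article gives neither a between-child coefficient of variation (CV) nor a rate of missed days, so both are assumed here, and counts are assumed to be summed over the week. Let *X* be the full-week total (mean 1, SD 0.25), and let a share *p* of children have it multiplied by 0.8. The variance is 1.0625 × E[*K*²] − (E[*K*])².
- *p* = 0.1: 1.0625 × 0.964 − 0.98² = 0.0639. Against 0.0625 this is a rise of 2.2%.
- *p* = 0.2: 1.0625 × 0.928 − 0.96² = 0.0644, a rise of 3.0%.
- Relative to the squared mean, the rises are 0.0639/0.9604 against 0.0625, about 6%, and 0.0644/0.9216 against 0.0625, about 12%.

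**Power, under stronger assumptions.** Suppose 2% to 10% of child-days are lost equally in both arms and add nothing to a weekly sum, with a CV of 0.2 to 0.4. With *q* the share of days lost, SD² = (CV² + 1)[*q*(1 − *q*)/5 + (1 − *q*)²] − (1 − *q*)², and the standardised effect is 0.5 × CV × (1 − *q*)/SD. It falls from 0.5 to between 0.49 (CV 0.4, *q* 2%) and 0.40 (CV 0.2, *q* 10%). Power with 108/1.68 = 64.3 effective children per group falls from 81% to between 80% and 62%.

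**Bias, if wear differed by arm.** A difference of 1% in mean wear shifts a total by 1% of the mean. That is 0.01/0.4 = 0.025 SD to 0.01/0.2 = 0.05 SD. A 2% difference gives 0.05 to 0.10 SD. No such difference is documented.

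**The case against.** The strongest reply is that this is a derivation detail that a condensed article may leave to its analysis plan, which is not shown. The 10-minute rule supplies exactly the wear time needed to form a rate or to drop short days, so nothing stated is wrong. This stands in part. A minimum number of valid days and the handling of missing days may well be set elsewhere, and their absence is not held against the article. What does not go away is that the article states a form for the count variable, a total, and gives a time-standardised form only to the intensity bands.

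Three stronger readings are tempting and should not be adopted.

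- **That absent days and removed belts are scored as inactivity.** No section says so. Defining non-wear suggests an intention to separate it from sedentary time. A child absent at 9.00 AM has no device fitted, so that day would naturally be missing. A sum over four days would still be lower than a sum over five, but if totals are analysed by day the absent day simply drops out.
- **That the primary variable is firmly a weekly total.** The abstract says counts, while Outcome measures and Data analysis are looser, and the period of summation is not given. Part-day removal lowers the total under either reading; the 20% figure needs the weekly one.
- **That the group comparison is biased.** Belts coming off around tyres and crates is conceivable but undocumented. The materials are used at recess, so the plausible loss is minutes, not days, and even a full hour is 3.3% of a weekly total if activity is even.

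Researcher fitting within a fixed window also limits how much wear can vary.

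**Conclusion.** The point holds as a modest defect in how the primary variable is defined. On the most natural reading of the article the count is a total, and the stated non-wear rule leaves a total unchanged. Under even activity, an unworn hour costs about 17% of a day's total or 3.3% of a week's. A missed day costs 20% only under weekly summation.

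The consequence that can be asserted is avoidable noise. Its size depends on a CV and on missed-day rates that the article does not give. On a weekly sum with a CV of 25% and 10% to 20% of children missing one day, raw variance rises by only 2% to 3%. A reader who adds only the variance of the missed-day deduction, *p*(1 − *p*) × 0.2² over 0.25², would get 6% to 10%; that leaves out the smaller spread among the affected children. The power loss down to 62% is the far end of an assumed range in which 10% of child-days are lost and between-child variation is low; it is not an expected value. Bias would need wear to differ by arm, and the document does not show that. The sample size stands.

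**What to change.** Define the primary count variable as counts per minute of device-derived wear time. Identify wear with the 10-minute zero-count rule already adopted, average over the days the child wore the device, and use the same definition at baseline and post-test. Report total counts descriptively, together with wear time by arm and by test week, so that any difference in wear can be seen.

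This takes one line in the endpoint definition and no new data collection. It should rest on the device record: the article gives nominal fitting and removal times but does not say that actual times are logged, and it mentions no attendance roll.

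The downsides are small. Ten minutes or more of true stillness would be classed as non-wear and would raise the rate slightly. Children with very little wear would be handled as missing. A rate also does not fully repair losses concentrated in active periods: if belts come off mainly at recess, counts per worn minute will still be somewhat low.

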#### Children's activities after school

We collect information about activities during after-school hours (between 3.30 PM and 7.00 PM) in both baseline and post-test sessions using a real-time activity diary. Responses to the activity diary are recorded at three random times for each of 4 consecutive week days. The activity diary consists of 12 questions (9 multiple choice, 3 Visual Analogue Scales [VAS]). The multiple choice questions determine who is recording the information, what the child is doing and using, who the child is with, if the television is on and whether they are indoors or outdoors. The VAS questions are used to estimate, 1) activity level, 2) frequency of movement and 3) intensity of involvement in an activity. Questionnaire items were developed from literature on children's after school activities and in conjunction with a workgroup of paediatric health care professionals, researchers working with young children, and parents of children in the relevant age group. The activities were chosen to represent activities in which 5- to 7-year-olds commonly engage during after-school hours. The aim was to create a questionnaire that could be answered in 1 to 2 minutes. Pilot testing revealed response time ranged from 0.5 to 3 minutes, with a shorter response time as respondents became increasingly familiar with the questions.

Parents record responses to diary questions on a Palm Pilot Z22 (Palm Inc., Sunnyvale, CA) loaded with Experience Sampling Program (ESP) software http://www.experience-sampling.org. For each diary entry, the Palm emits a signal that continues for 3 minutes before the device is switched off and the entry is marked as a non-response. Once the survey commences, a 3-minute lag of non-activity is allowed to accommodate interruptions before switching off. Any questions completed prior to the non-activity are saved.

##### Protocol

Parents are instructed in use of the Palm in a personal meeting with the researchers or through a step-by-step instruction sheet included with the Palm pilots when they are distributed to the parents. Parents are provided with a contact number, should they encounter any problems with the devices. On the morning of first day of data collection, researchers activate the software and place the devices in the participating children's schoolbags together with the accompanying information and written instructions. After the 4 days of data collection, parents return the Palm Pilot to their child's school. Data from the Palm Pilots are downloaded onto PCs using the ESP desktop software and stored as .txt files.

#### Videotaping

Digital hard drive video cameras (Sony DCR-SR65, http://www.sony.com.au) are used together with Bluetooth wireless microphones (ECH-HW1, http://www.sony.com.au) to capture social interactions and what the children are doing during recess. Children are videotaped for 15 minutes during recess by an unobtrusive camera person who does not interact in any way with the children. No videotaping occurs during bad weather when the children are indoors during recess; researchers also avoid taping children during lunch or snack time. The videos are transferred to computers using the accompanying software and stored as .mpg files. After conversion to .mov files, the resulting data are coded using Studio Code (v 4.2.4, http://www.studiocode.com). The coding scheme is developed specifically for this study and captures categories of play and non-play, as well as quantification of social interactions.

#### Children and Teachers' Perceptions of Competence and Social Acceptance

The Pictorial Scale of Perceived Competence and Social Acceptance for Young Children (PSPCSAYC) (Harter and Pike, 1984) [60] is included to assess two domains of competence (physical and academic) and two domains of acceptance (peer and maternal). Administration of the PSPCSAYC to children involves responding to four choices elicited by presenting paired pictorial items featuring children who are skilled or less skilled in a particular domain and asking who the child is most like. Further probing occurs to see if they see themselves as a lot like the child or just a little. The questions are devised to guard against generation of socially desirable responses.

The teacher rating scale involves a description of specific skills in each domain, with the exception of maternal acceptance. Teachers respond using a 4-point scale. The PSPCSAYC is widely used. For example, the original article describing the scale has 374 citations in Scopus (21 July, 2011).

#### Social Skills Improvement System - social skills

The Social Skills Improvement System Rating Scales (SSIS-RS) [61] are a revision of the widely used Social Skills Rating System (SSRS) [62]. For children below 8 years of age, parent and teacher reports of behaviours, using a 4-point scale, are used to assess Social Skills (i.e., communication, cooperation, assertion, responsibility, empathy, engagement, and self-control); and Problem Behaviours (i.e., externalizing, bullying, hyperactivity/inattention, internalizing, and autism spectrum).Teacher reports also includes an Academic Competence subscale. The SSIS-RS has been specifically designed for pre- and post-intervention assessment. Significant re-norming was conducted in the revision from the SSRS [62]. Protocols described in the SSIS-RS manual, such as ensuring the rater has known the child for at least 2 months, are followed. Parents of the children are provided with feedback on their child's score and in cases of extreme scores, are offered follow-up with the psychologist on this project. The completion time is 10 to 25 minutes per form. Compensation of teachers' time is offered by paying the schools for relief teaching staff. Scores are entered manually into the SSIS Assist software http://www.pearsonpsychcorp.com.au.

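### In intervention schools the SSIS-RS raters are themselves offered the risk-reframing session and know the allocation at post-test, so a shift in their ratings would appear as a treatment effect on social skills.

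*Protocol article*

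**What the plan says.** The section on the Social Skills Improvement System says that, for children under 8, "parent and teacher reports of behaviours, using a 4-point scale, are used to assess Social Skills"; problem behaviours, including bullying, are rated by the same adults. Table 1 schedules one rating at baseline and one at post-test. The self-concept scale (PSPCSAYC) has a teacher form and a form that a researcher administers to the child.

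Under Adult intervention: Risk Reframing, "Teachers and parents of participating children from the intervention schools are asked to participate in a 2-hour group intervention", where they examine "their beliefs regarding the benefits and risks associated with active play". Of control schools the article says that "they do not have access to the unstructured materials or to risk reframing". Under Randomisation, "The schools are informed of their allocated treatment after baseline data collection".

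For after-school time, "Parents record responses to diary questions on a Palm Pilot Z22". The diary has 12 questions: nine are multiple choice and three are visual analogue scales. "The VAS questions are used to estimate, 1) activity level, 2) frequency of movement and 3) intensity of involvement in an activity".

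Social interaction at recess is also filmed for 15 minutes. "The coding scheme is developed specifically for this study and captures categories of play and non-play, as well as quantification of social interactions".

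The Data analysis section plans mixed-effects regression of net change from baseline between groups. It names social skills and after-school activities among the outcomes on which effectiveness will be judged.

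**The concern.** This goes further than an ordinary lack of blinding. One of the two intervention strategies is aimed at how parents and teachers see children's play, and these adults then score the child. Treatment can therefore act on the rater as well as on the child, and in one arm only. At baseline the raters do not know the allocation; at post-test they can.

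Social skills appear in the trial's title and in its stated aim. If an SSIS-RS difference were taken alone as evidence that children's social skills improved, it could not be told from a change in how treated adults score the same behaviour.

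**Working it through.** **Step 1: who rates, and who is treated.** From the sections cited above:

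| Measure | Completed by | Raters offered the session (intervention arm) | Raters can know allocation at post-test |
|---|---|---|---|
| SSIS-RS | Parents, teachers | Yes | Yes |
| PSPCSAYC, teacher form | Teachers | Yes | Yes |
| After-school diary | Parents | Yes | Yes |
| PSPCSAYC, child form | Child, with a researcher | No | Researcher blinding ends at each school after baseline |
| Recess video | Coders, not described | No | Not stated |
| Accelerometer | Device | Not applicable | Not applicable |

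**Step 2: what net change estimates.** Let δ be the true effect on the child and b the rating shift in the intervention arm, both in SD units. Under randomisation the expected baseline difference is 0. The expected post-test difference is δ + b. Net change is therefore (δ + b) − 0 = δ + b. Baseline adjustment does not remove b, because b arises after baseline and in one arm only.

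**Step 3: the plan's own figures.** Sample size section: effect 0.5 SD, significance level 0.05 (taken as two-sided), power 80%, ICC 0.04, 18 children per school, 6 schools per arm.
- Unadjusted: the two-sample t-test needs 63.8, so 64 per group, as stated.
- Design effect: 1 + (18 − 1) × 0.04 = 1.68.
- Adjusted: 64 × 1.68 = 107.5, so 108 = 6 × 18 per group, as stated.

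The figures reproduce.

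**Step 4: illustration of size.** Three inputs are assumptions: the shift b, the use of the activity ICC of 0.04 for the SSIS-RS, and a comparison at post-test only.
- Standard error = √(2 × ((1 − 0.04)/18 + 0.04)/6) = √(2 × 0.0933/6) = √0.0311 = 0.176 SD.
- The chance of a two-sided significant result with δ = 0 comes from the noncentral t distribution on 12 − 2 = 10 df, with noncentrality b/0.176.

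| Assumed b (SD) | Chance of a significant result, 10 df | Same, normal test |
|---|---|---|
| 0 | 5% | 5% |
| 0.1 | 8% | 9% |
| 0.2 | 18% | 20% |
| 0.3 | 34% | 40% |

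The planned analysis uses change from baseline. Its standard error depends on the baseline to post-test correlation, which is not given, and could be larger or smaller than 0.176.

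**Step 5: the diary.** The nine multiple-choice items record matters such as what the child is doing, with whom, whether the television is on, and indoors or outdoors. They are answered at random prompts close to the event. A shift in attitude can plausibly move mainly the three visual analogue items. If treated parents in fact allow more outdoor play after school, that is an effect the adult intervention seeks and belongs to δ, not b.

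**The case against.** The strongest case against runs as follows. No stated figure is wrong and no passages conflict. A single two-hour discussion of play and risk need not change how an adult scores communication, cooperation or empathy, and the documents do not show that it does. Adults are asked to attend, so some raters will not have done so. For this age group the article describes only adult reports on the SSIS-RS. The trial already triangulates: Table 1 places video-coded playground behaviour beside the SSIS-RS under social interaction, and the child also answers the self-concept scale. Only secondary outcomes are touched.

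Much of this stands, and it limits the size of the point. It does not remove the point: adults who did not attend can still know the allocation, and the planned analysis cannot estimate or exclude b, whether it is small or large.

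Three stronger readings are tempting, and the documents do not support them.
- A reader might infer that post-test video is coded by unblinded researchers, because researcher blinding ends at each school after baseline. The Videotaping section does not say who codes or whether clips are masked, and an article may leave that to the full protocol.
- A reader might infer that the social claim rests mainly on treated raters. The article gives no order among its social measures, and the video is one of them.
- A reader might infer that the video and the child's own report should outrank the SSIS-RS. The video is a study-specific code of 15 minutes of recess and covers a narrower construct than a normed scale. The child form measures self-concept, and it is administered by researchers who are no longer blinded to the school's allocation.

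**Conclusion.** The point holds for the SSIS-RS and the teacher form of the self-concept scale, and mainly for the three visual analogue items of the diary. On these, a post-baseline rating shift in one arm would be reported as a treatment effect, and the net-change analysis cannot remove it. The accelerometer primary outcome is unaffected.

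The size is unknown. The 8%, 18% and 34% show how a modest shift would matter in a trial of this size. They rest on an assumed shift, an ICC quoted for activity, and a post-test-only standard error, so they do not describe the planned test. The conclusion concerns what an SSIS-RS difference can support on its own. It is not that the instrument should be dropped or demoted.

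**What to change.** 1. State in the protocol or analysis plan that the SSIS-RS, the teacher PSPCSAYC and the diary's visual analogue items are unblinded ratings by adults who, in one arm, were offered part of the intervention.
2. State that improved social skills in children will not be concluded from the SSIS-RS alone. It is to be read jointly with the video-coded social interaction, with neither ranked above the other.
3. Keep the existing video coders unaware of school and arm as far as the footage allows: fix the coding scheme on baseline footage, remove school and arm labels, and code clips in random order.

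The cost is a few sentences of text and some file handling; no new data are needed. The downside is that the video is a noisy 15-minute sample of a narrower construct, so it may fail to corroborate a real SSIS-RS effect. Play materials visible in the clips will also make masking only partial.
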